#### Data security and confidentiality

SAMRC security policy has been operational since 2017, ensuring standard methods and procedures are used so that security issues can be addressed expediently with minimum impact on quality. Due to the sensitivity of mother-infant data, the most secure options will be implemented: (i) SSL/https, to ensure data transmissions over the Internet are encrypted; (ii) nginx/reverse proxy, to provide another security layer between the web server and the Internet; (iii) No server-side caching, to avoid malicious manipulation of URLs. The following measures should also be put in place: (i) database encryption; (ii) hosting contractor will confirm the use of encrypted drives for the databases. The main risk to data security and confidentiality is from external users accessing personal data. To mitigate this risk, data will be pseudoanonymised before transfer and transferred using encrypted files.

#### Data sharing and access

The SAMRC has a data repository that is created on demand for each study. The repository is password-protected, and only designated individuals with the link have access to content. Data will be anonymised when stored in the repository.

##### Data sharing

Data will be shared among the Study Investigators and the study statisticians, after cleaning has been completed, in order to proceed with the analyses and results dissemination.

##### Governance of access

Anyone wishing to access the data during the study or after should write to the coordinating and co-investigators (CIs) with an outline of the analysis they would like to undertake. The CIs will then decide whether to grant access to the data to this researcher and inform the researcher within one month of the application receipt.

#### Statistical methods

The statistical analyses of the PedMAb phase I trial will be performed, unblinded as to study arm, on the “safety analysis dataset” including infants who will have received at least one dose of the randomized bNAb (alone or in combination) and who have either presented a SAE grade 3–4 during the first 28 days following first or second bNAb administration or who have completed the same follow-up with safety assessment.

The analyses will be also performed according to the per-protocol (PP) principle. The PP analysis dataset will comprise infants who have received the expected dose(s) of the randomized bNAb (alone or in combination) and who have completed all their follow-up visits (6 months) since the first or second bNAb administration.

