**Day 28 safety assessment**								

#### Study population

Recruitment shall occur when women access antenatal clinic care from 34 weeks of gestation or post-delivery. The clinical research site has experience working with at-risk populations, given the 43% antenatal HIV prevalence in the district, and will develop a site-specific recruitment plan. Interested pregnant women will be offered an informal discussion with the site clinical research nurse or counselor. This discussion will protect the HIV status, medical information and personal circumstances of the antenatal potential participant. The potential participant or post-delivery mother will be informed about the study and will be given a copy of the Participant Information Sheet and consent form. They will have the opportunity to ask questions. Community staff will also speak with pregnant women in the community to publicize the study, and if the pregnant women are willing to attend the clinical research site post-delivery, they will be offered enrolment into the study. Mothers will only be enrolled post-delivery.

The informed consent procedure will follow Good Clinical Practice (GCP). Postnatal consent will occur for those women who have not been consented antenatally. For mothers who consent antenatally, and for mothers who consent postnatally (within 96 h), screening procedures will be undertaken. Following the receipt of screening results the mother-baby pair will be identified as eligible for enrolment or not. A checklist will be completed for all eligible mothers confirming their understanding of the study and confirming participation in the study. At this stage the mother will be provided an opportunity to withdraw from the study before the dose of study medication is administered. There is a 96-h window after delivery for women to be enrolled. This option must be balanced by the knowledge that the product is more likely to work the sooner it is administered after exposure (delivery). The timeline between randomization and study product administration will be minimized to avoid any randomized untreated infant; however, an infant will be considered enrolled in the study when he/she has received study product.

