#### Randomization and blinding

In arm 1 and 6/6b neonates exposed to HIV and born negative will be sequentially recruited, while in arms 2 or 4 and arms 3 or 5 further exposed neonates without HIV will be allocated in a ratio 1:1 using a randomization list that will be computer-generated by the trial statistician and provided through a paper-based envelope approach. The randomization list will be stratified in permuted block of size of 4; it will be used in step 1 (arms 2 to 5 only).

The trial is single-blind with neonates’ mothers blinded with respect to study product allocation to minimize the potential of contamination between arms (mothers allocated to one bNAb study product and willing to change to benefit from the other bNAb) and maximize an objective measurement of the primary outcome. We chose not to design a double-blind trial because doses within groups will be administered in a sequential way; this condition implies that even if the study staff does not know the exact dose administered, they will still be able to guess that the doses gradually administered are in increasing quantities, and, thus, eliminating at least in part the advantage of the double-blind design.

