#### Descriptive and univariate analyses

All the available safety data of each participant will be considered in the analyses; these data will be classified as severity (grade), expectedness, and potential relatedness (causality) to the study intervention. Descriptive analyses will be performed according to the study arm and the endpoints will be summarized using means with standard deviations or medians with interquartile ranges or ranges or 95% confidence intervals (CI) for quantitative variables, and proportions with their 95% CI for qualitative or categorical variables; CIs will be calculated using the exact method.

Given the small sample size of the study arms, there will be no statistical power for a formal test of differences between study arms with respect to safety. The analyses will check for clinically relevant differences in the main baseline maternal and infant characteristics between the following study arms: 2 vs 3, 4 vs 5, 6 vs 3 and 5; the presence of relevant imbalances in these characteristics among arms will be eventually tested by calculating differences [between means (standardised effect size) or proportions] with the corresponding 95% confidence intervals.

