#### Toxicity management and enrolment in study arms

Arm 1 will follow a sequential recruitment, and all the other arms will be randomized. Simultaneous recruitment will occur for arms 2 and 4; arms 3 and 5; and will proceed as follows:

When the planned 8 infants of arm 1 have been enrolled, given study product and completed 28 days of follow-up, the study investigators will review interim safety data; there will be a 1-month pause in the enrolment and administration of subsequent doses (arms 2 and 4) during this review. If review of safety data reveals Grade 3 or higher AE possibly, probably, or definitely related to product administration, the study investigators will decide to consult with the ISMC. If review of safety data reveals no SAE, enrolment into subsequent dose arms will be opened. The same work-flow will apply to arm 2 and 4, arms 3 and 5, and arm 6. Infants enrolled in arm 6 will be treated with a second administration of bNAbs after 3 months constituting arm 6b; these babies will be followed according to the criteria described in the following paragraph.

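### Safety dataset entry is tied to the randomised product: the wrong word for arms 1 and 6/6b, and in arms 2 to 5 it drops a wrong-product infant from the primary safety proportion

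*Protocol article*

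**What the plan says.** All references are to the protocol article.

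- **Statistical methods, safety dataset.** An infant must have "received at least one dose of the randomized bNAb (alone or in combination". The infant must also have had a grade 3–4 SAE in the 28-day window "or who have completed the same follow-up with safety assessment".
- **Statistical methods, per-protocol dataset.** This takes "infants who have received the expected dose(s) of the randomized bNAb" with all visits to 6 months completed.
- **Randomization and blinding.** "In arm 1 and 6/6b neonates exposed to HIV and born negative will be sequentially recruited". The randomisation list serves arms 2 to 5 only, 1:1, by paper envelope. The abstract and Table 1 agree.
- **Toxicity management and enrolment in study arms.** "Arm 1 will follow a sequential recruitment, and all the other arms will be randomized".
- **Study population.** "an infant will be considered enrolled in the study when he/she has received study product".
- **Descriptive and univariate analyses.** "All the available safety data of each participant will be considered in the analyses". Confidence intervals are exact.
- **Primary endpoint; Primary analysis on primary endpoint.** The endpoint is the proportion with at least one related Grade 3 or higher AE within 28 days. It applies to every arm and is reported by arm.

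**The concern.** A safety population normally follows exposure: whoever received the product is counted, under what they received. Here entry depends on having received the product that was randomised. That raises two questions.

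The first is whether the word fits arms that were never randomised. The second is what happens to an infant in arms 2 to 5 who receives the wrong product. Each randomised pair sets one antibody against the other (arm 2 against arm 4, arm 3 against arm 5), so any swap within a pair is a wrong-product error and not merely a wrong dose.

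At stake is the main output of the trial, a by-arm safety proportion on about 8 infants, including the first paediatric use of CAP256V2LS. At that size, one related event that goes uncounted changes an arm's result.

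**Working it through.** **1. The plan's own numbers.** Target 6 per arm with 25% loss: 6 / (1 − 0.25) = 8. There are six cohorts, because arm 6b is the same infants as arm 6: 6 × 8 = 48. This reproduces the stated enrolment. The sample size section expects these arms in the final safety dataset.

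**2. Which arms have a randomised product.** Arms 2 to 5: 4 × 8 = 32. Arms 1 and 6/6b: 8 + 8 = 16 with none. The abstract, Table 1 and the randomisation section agree on this. The toxicity management section does not, since its sentence would make arm 6 randomised.

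**3. Is arm 1 or arm 6/6b meant to be left out?** No. The safety definition itself mentions combined administration and a second administration, and only arm 6/6b has either. The primary endpoint is stated for all arms. The primary analysis covers each step. Baseline characteristics of arm 6 are to be set against those of arms 3 and 5.

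**4. An infant randomised to arm 2 but given the arm 4 product.**

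| Rule | Result |
|---|---|
| Enrolled (Study population) | Yes: study product was received, and assignment is not mentioned |
| Safety dataset | No: the randomised product was not received |
| Per-protocol dataset | No, and properly so |
| AE rates per person-time (Secondary analyses) | Yes: estimated among enrolled neonates |
| By-arm primary proportion | Absent from both arms |

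No sentence places this infant by product received. An infant given a wrong dose of the right product stays in the safety dataset and leaves only the per-protocol dataset.

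**5. Size, for one infant (an assumption).** With zero events in n infants, the exact two-sided 95% upper limit is 1 − 0.025^(1/n).

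- n = 8: 1 − 0.025^(1/8) = 36.9%
- n = 7: 1 − 0.025^(1/7) = 41.0%

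The probability of seeing at least one event at an assumed true rate of 10%:

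- n = 8: 1 − 0.9^8 = 57.0%
- n = 7: 1 − 0.9^7 = 52.2%

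**6. Where the event goes.** Suppose the misallocated infant has a related Grade 3 event, nobody else does, and 8 are assigned to each arm of the pair.

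| Rule | Arm assigned | Arm whose product was received |
|---|---|---|
| As written | 0/7 | 0/8 |
| By product received | 0/7 | 1/9 = 11.1% |
| By assignment, for comparison | 1/8 = 12.5% (exact CI 0.3% to 52.7%) | 0/8 |

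The assigned arm falls to 7 under the current wording and under analysis by product received alike. What the current wording adds is that the event appears in neither arm.

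**The case against.** The strongest reply is that *randomized* is a loose word for *assigned*, and that no analyst would drop two cohorts because of it. That stands. A reader might infer from the literal text that 16 of 48 infants (33%) fall outside the safety result. The documents do not support this, for the reasons in step 3.

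A reader might also infer that a misallocated infant is analysed nowhere. That is too strong. The person-time AE rates cover enrolled neonates, and enrolment depends only on receiving study product. The first pause trigger under Analyses and stopping rules covers any infant. The statement that all available safety data will be considered points the same way, although it does not say in which arm such an infant would be counted.

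The per-protocol exclusion is no error, since leaving out wrong-product infants is what such a set is for.

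Misallocation is hypothetical: the article reports none and gives no rate. One infant in each of arms 2 to 5 would mean 4 of 32 (12.5%), and nothing supports a rate that high. Handling of dosing errors is often left to the SAP. Here, however, the article itself states the entry rule, and read strictly that rule removes the infant from the primary by-arm result.

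The event-or-completion condition in the same sentence is a separate issue. Correcting it would not correct this one.

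**Conclusion.** The point holds in limited form and is minor. For arms 1 and 6/6b it is a wording defect with no loss of infants intended, together with a contradiction between sections on whether arm 6 is randomised. For arms 2 to 5 the stated rule departs from exposure-based safety analysis. A wrong-product infant, with any related Grade 3 or higher AE, drops out of the primary by-arm proportion, and no text puts that infant back.

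The size depends on misallocation occurring. With one infant lost from a zero-event arm, the exact upper limit moves from 36.9% to 41.0%. The more important consequence is that an event in that infant would show in no arm. Both figures rest on the assumption of one affected infant and 8 infants otherwise evaluable per arm.

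**What to change.** 1. In Statistical methods, state the exposure condition of the safety dataset as: *at least one dose of any study bNAb, analysed by product and dose actually received, in all arms (1 to 6/6b)*.
2. In the per-protocol definition, replace *randomized* with *assigned*. Arms 1 and 6/6b then qualify, and wrong-product infants remain excluded.
3. Reconcile the sentence under Toxicity management and enrolment in study arms with the abstract, Table 1 and Randomization and blinding, so that only arms 2 to 5 are called randomised.

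The cost is a few words in two sections, with no extra infants, visits or data. The one drawback is that a misallocated infant makes arm denominators depart slightly from 8, for example 7 and 9 after a single swap, which a footnote to the safety table can explain.

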##### Primary endpoint

The primary endpoint, applying to all the primary objectives, is the proportion of participants who develop at least one ≥ Grade 3 AE, including local and systemic reactions, lab toxicities, and/or clinical events, that is possibly, probably or definitely related to each bNAb any time from the first day of study product administration through further 28 days following bNAb(s) administration (all arms).

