#### Primary analysis on primary endpoint

The primary endpoint of each step is the proportion of neonates who develop at least one ≥ 1 Grade 3 adverse events (AE) possibly, probably or definitely related to each bNAb that occurred within 28 days after a first or a second dose of bNAbs administration (alone or in combination). The primary endpoint will be described according to the study arm, using proportions with the corresponding 95% CI.

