## Abbreviations

ADA: Anti-bNAb antibody
AE: Adverse events
ALT: Alanine aminotransferase
ART: Antiretroviral therapy
ARV: Antiretroviral (prophylaxis)
AST: Aspartate aminotransferase
AUC: Area under the curve
bNAbs: Broadly neutralizing (anti-HIV-1 monoclonal) antibodies
CAP256V2LS: A broadly neutralising anti-HIV-1 monoclonal
CAPRISA: Centre for the AIDS Programme of Research in South Africa
CD4: A receptor (or a T-cell lymphocyte with many such receptors)
cGMP: Current good manufacturing practice
CHO: Chinese Hamster Ovary DG44 cell line
CI: Confidence intervals
C_max_: Maximum plasma concentration
CRF: Case report form
CRO: Clinical research organisation
CRS: Chatsworth Clinical Research site
DBS: Dried blood spots
DSMB: Data safety and monitoring board/committee
e-CRF: Electronic case report form
ELISA: Enzyme-linked immunosorbent assay
EOT: End-of-trial visit
FBC: Full blood count
FDA: U.S. Food and Drug Administration
GCDMP: Good clinical data management processes
GCP: Good clinical practice
GMR: Geometric mean ratio
GPT: Glutamic pyruvic transaminase
HBIG: Hepatitis B immunoglobulin
HIV-1: Human immunodeficiency virus type 1
IgG1: Recombinant human immunoglobulin
IND: Investigational new drug application
ISMC: Independent safety medical committee
ISSC: Internal study safety committee
MTCT: Mother-to-child-transmission of HIV-1
NCA: Non-compartmental analysis
NIAID: National Institute of Allergy and Infectious Diseases
NICU: Neonatal intensive care unit
NIH: National Institutes of Health
PCR: Polymerase chain reaction
PI: Principal investigator
PK: Pharmacokinetics
PMTCT: Prevention of mother-to-child-transmission of HIV-1
POC: Point-of-care (test)
PrEP: Pre-exposure prophylaxis
REDCap: Research Electronic Data Capture
SAE: Serious adverse event
SAMRC: South Africa Medical Research Council
SAHPRA: South African Health Products Regulatory Authority
SC: Subcutaneous injection
SOA: Schedule of activities
UIC: Unique identifier code
VRC07-523LS: A broadly neutralising anti-HIV-1 monoclonal
V1V2-glycan: HIV envelope variable loop 1 and 2 glycan
VRC: Vaccine Research Center
WHO: World Health Organization

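### The safety analysis dataset selects infants on outcome, using an event that is not the primary endpoint

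*Protocol article*

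**What the plan says.** All references are to the protocol article.

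- **Primary endpoint.** The measure is "the proportion of participants who develop at least one ≥ Grade 3 AE", with local and systemic reactions, laboratory toxicities and clinical events all included, "that is possibly, probably or definitely related to each bNAb any time from the first day of study product administration" through a further 28 days. Seriousness is not required, and the grade has no upper limit.
- **Primary analysis on primary endpoint.** The event is restated with the window "that occurred within 28 days after a first or a second dose of bNAbs administration".
- **Statistical methods.** The analyses are run on a safety analysis dataset "including infants who will have received at least one dose of the randomized bNAb" and "who have either presented a SAE grade 3–4 during the first 28 days" after the first or second administration, "or who have completed the same follow-up with safety assessment". The qualifying event has no relatedness condition.
- **Abbreviations.** The list gives "SAE: Serious adverse event" as an entry separate from AE.
- **Sample size calculation.** Eight infants are enrolled per arm, with 6 targeted for the final safety dataset at 25% loss to follow-up. Under Study population, an infant counts as enrolled only once dosed, so anyone missing from the dataset has been exposed.

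**The concern.** A safety population is normally everyone exposed. Here exposure is not enough: the infant must also have had a particular event or have stayed to day 28. That raises two problems.

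First, the event that lets an early leaver in is not the event being counted. Tables 4 and 5 schedule laboratory safety assessments at days 3 and 14, so a related Grade 3 laboratory result can be on file before an infant leaves. If it is not serious, the infant meets neither entry route and disappears from both numerator and denominator.

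Second, whatever SAE was intended to mean, membership depends on outcome. An early leaver with a qualifying event is kept, and an early leaver without one is removed.

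The proportion affected is the trial's primary result, reported by arm. With 8 infants per arm, one infant is 12.5 percentage points, and removing one can turn an observed related toxicity into a reported 0%.

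**Working it through.** **Inputs.** From the document: 8 dosed per arm, 25% loss, target 6, exact confidence intervals (Descriptive and univariate analyses). Assumed: the true event rate p, and the share s of endpoint events that also meet the SAE grade 3–4 route. The protocol gives neither.

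**The plan's own figure.** 6 / (1 − 0.25) = 8 per arm, and 6 arms × 8 = 48 (arm 6b is the same infants as arm 6). This reproduces. At 25% loss, 8 × 0.25 = 2 dosed infants per arm fall outside the dataset.

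**Single-arm examples (Clopper-Pearson 95% CI).** Eight infants are dosed, and one has a related, non-serious Grade 3 event and leaves before day 28.

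| Rule | One early leaver | Two early leavers, the second event-free |
|---|---|---|
| As written | 0/7 = 0% (0 to 41.0%) | 0/6 = 0% (0 to 45.9%) |
| Endpoint event or completer | 1/8 = 12.5% (0.3 to 52.7%) | 1/7 = 14.3% (0.4 to 57.9%) |
| All dosed infants | 1/8 = 12.5% (0.3 to 52.7%) | 1/8 = 12.5% (0.3 to 52.7%) |

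**How often an endpoint infant would be dropped.** With loss d independent of the event, the chance of at least one in an arm of 8 is 1 − (1 − p·d·(1 − s))^8.

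| d, s | p = 5% | p = 10% | p = 25% |
|---|---|---|---|
| 25%, 0 | 9.6% | 18.3% | 40.3% |
| 25%, 0.5 | 4.9% | 9.6% | 22.4% |
| 10%, 0 | 3.9% | 7.7% | 18.3% |

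These are on the high side, because they place all loss before day 28 and after the event.

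**Bias, SAE read literally.** An event infant is kept with probability (1 − d) + d·s and an event-free infant with probability 1 − d. With s = 0 the expected proportion is p(1 − d) / [p(1 − d) + (1 − p)(1 − d)] = p. Observed events are discarded, but the expectation does not move unless infants with such events are more likely to leave.

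**Bias, SAE read as severe adverse event.** Every endpoint infant is kept, so the expected proportion is p / [p + (1 − p)(1 − d)]. At d = 25%:

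- p = 10%: 0.10 / (0.10 + 0.90 × 0.75) = 0.10 / 0.775 = 12.9%.
- p = 25%: 0.25 / (0.25 + 0.75 × 0.75) = 0.25 / 0.8125 = 30.8%.

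This assumes that leavers' events are seen before they leave and that no early leaver has an unrelated Grade 3–4 event. Such an infant would be kept as a non-event and would reduce the inflation.

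**Bias of the all-dosed set.** If every leaver goes before any event, the expected proportion is p(1 − d): 10% reads 0.10 × 0.75 = 7.5%. If leavers' events are all seen first, it is p. Under independent loss, the all-dosed estimate is therefore at or below the true rate, and the endpoint-event-or-completer estimate is at or above it.

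**The case against.** The strongest reply is that SAE is loose wording. Toxicity management and enrolment in study arms uses Grade 3 or higher related events and absence of an SAE almost as complements, and Sample size calculation speaks of SAE rates although the endpoint is graded adverse events. This is plausible, and it removes most of the dropped-event case. It does not remove the selection on outcome.

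A second reply is that event-or-completed-window is a recognised evaluable set, that its upward bias is cautious for a safety trial, and that keeping early leavers as non-events biases downward. All of that is true. It argues for showing both estimates, not for making the selected set the only safety set. The per-protocol set does not help, since it requires all visits to 6 months.

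Third, observed events are not lost to the trial. Adverse event rates per person-day are estimated among enrolled infants, all available safety data are to be considered, and completeness at day 28 is to be reported. This limits the harm, but none of these statements redefines the dataset for the primary proportion. Loss is also expected to be minimal, although the same section (Missing data/loss to follow-up) repeats the 25% allowance.

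A reader might infer more than the document supports:

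- **That deaths are excluded.** This needs a fatal event to be graded above 4. The article mentions no such grade, the grading table it cites is not at hand, and an infant who dies may already have had a qualifying event.
- **That Grade 4 events are not counted.** Primary analysis on primary endpoint has "1 Grade 3 adverse events (AE) possibly, probably or definitely related to each bNAb" preceded by a stray inequality sign. The Primary endpoint section is clear, so this is clerical.
- **That the sequential arms 1 and 6/6b are left out** because the dataset refers to a randomised product. The same sentence covers combination dosing, which occurs only in arm 6/6b. This too is clerical.
- **That safety oversight is compromised.** The pause triggers under Analyses and stopping rules count infants in each arm and do not use this dataset.
- **That the whole trial is the first in neonates.** Study products says only that CAP256V2LS was never tested in pediatric populations.

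**Conclusion.** The point holds for the reported primary estimate. The dataset is conditioned on outcome, and its qualifying event does not match the primary endpoint. Only infants who leave before completing 28 days are affected.

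On the literal reading, one such infant with a related, non-serious Grade 3 or higher event takes an arm from 12.5% to 0%. On the looser reading the proportion is biased upward, by about 2.9 points at an assumed true 10% with 25% independent loss. The direction therefore depends on what SAE means and on who leaves, and no single direction of bias can be claimed. The event rates are assumptions, and 25% is the protocol's planning allowance, not an expected loss. Because the wording can produce a wrong primary result and costs little to change, it should be corrected before the primary analysis.

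**What to change.** In Statistical methods, define the safety set as every infant who received at least one dose of bNAb, analysed by product and dose received, with no condition on events or completion. For arm 6b, use every infant given the second dose. Count every observed, at least possibly related event of Grade 3 or higher in the 28-day window, including any fatal event.

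State that event-free early leavers count as non-events and that this biases the proportion downward. Report their number per arm, and give a sensitivity analysis restricted to infants with an endpoint event or completed day-28 follow-up. Replacing SAE by the endpoint event alone is not enough, because the selection on outcome would remain.

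In the same edit, align the wording in Primary analysis on primary endpoint with Primary endpoint, and refer to the assigned rather than the randomised product in the dataset definitions. In Sample size calculation, describe the 6 as infants expected to complete follow-up, not as the size of the safety dataset.

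The cost is a few sentences of text and one extra descriptive row per arm. No new data or change in sample size is needed.
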